### Aims of the trial

The aims of current pragmatic trial are to test whether a 12-month multidimensional lifestyle intervention, including aspects of increased awareness of own lifestyle and related risks, motivation, self-management, diet, exercise, and a supportive environment, is (cost-)effective in reducing cardiometabolic health and decreases depressive and negative symptoms. Also, barriers and facilitators in implementing the intervention on nurse and patient level will be explored.

The primary research question is:Is a 12-month multi-dimensional lifestyle approach including a web tool for SMI patients effective in improving or stabilising abdominal obesity (waist circumference) and other cardiometabolic risk factors in SMI patients after six and twelve months intervention compared to care as usual?

Secondary research questions are:2.Is a 12-month multi-dimensional lifestyle approach including a web tool for SMI patients effective in reducing depressive and negative symptoms in SMI patients after six and twelve months intervention compared to care as usual?3.Is a 12-month multi-dimensional lifestyle approach including a web tool for SMI patients aimed at improving or stabilising abdominal obesity (waist circumference) and other cardiometabolic risk factors in SMI patients after six and twelve months intervention compared to care as usual, cost-effective?4.What barriers and facilitators on nurse and patient level affect implementation of the 12-month multi-dimensional lifestyle approach?

We hypothesize that this 12-months multi-dimensional lifestyle approach will improve cardiometabolic risk factors compared to patients who receive care as usual. Specifically, we expect the intervention to reduce waist circumference (WC), Body Mass Index (BMI) and Metabolic Syndrome Z-score (MS Z-score) after six and twelve months intervention because we expect that patients will try to increase their physical activity levels and improve their dietary habits. We expect that, through the intervention, patients will increase levels of physical activity and experience improvements in self-management skills and thereby improving self-efficacy [3, 14, 26], leading to a decrease in depressive [27] and negative symptoms [28] (i.e. lower depressive and negative symptoms scores). We hypothesize that the intervention will be cost-effective as costs will be relatively low (training of staff) while the physical and mental health of SMI patients will improve. Improvements in health, due to the increased self-management and increased exercise, might lead to less psychotropic drug use, such as antidepressants and anxiolytics [27, 28]. Finally, we will explore what barriers and facilitators on patient and nurse level have an influence on intervention implementation.

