### Outcomes

Measurements are performed on patient and staff level. An overview of all measurements at baseline, six and twelve months is given in Table 4.

**Table 4 Tab4:** LION trial measurement overview

		Baseline	6 months	12 months
Measurements on patient level				
Routine Outcome Monitoring				
General information	Birth year, gender, diagnoses, year of first psychosis	X		
	Medication use	X		X
Physical measures	Height	X	X	X
	Weight	X	X	X
	Waist circumference	X	X	X
	Blood pressure (systolic, diastolic, pulse)	X	X	X
Lab test	Lipids (Total cholesterol, LDL-cholesterol, HDL-cholesterol, triglycerides)	X	X	X
	Glucose metabolism (glucose, HbA1c)	X	X	X
Psychological measures^b^	CDSS	X		X
	PANSS	X		X
	HoNOS	X		X
	MANSA	X		X
Cost-effectiveness^a^	Dutch care consumption questionnaire	X	X	X
	SF6D	X	X	X
Web tool TLM				
Lifestyle habits	Daily physical activity (SQUASH)	X	X	X
	Food frequency questionnaire (adapted to patient population)	X	X	X
Additional measure by research assistant				
	Physical activity (pedometers) and body fatness^c^	X	X	X
Measurements on staff level				
General information	Birth year, gender, level of education, number of years working in psychiatry, function	X		
Staff questionnaire	Knowledge on diet and physical activity, attitude towards lifestyle changes in patients, self-efficacy in addressing lifestyle issues with patients	X		X
	Daily physical activity (SQUASH)	X		X
	Food frequency questionnaire	X		X

^a^ Measures are not part of standard ROM screening but added to ROM screening for the purpose of this study. ^b^ The conducted psychosocial measures within the ROM protocol could vary per team, not all teams conduct every psychosocial measure. ^c^ Only conducted by one of the five health care organisations (GGZ Friesland)

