#### Measurements on patient level

Most measures on patient level are conducted during the ROM screening, which is part standard care and of the scientific ongoing PHAMOUS (Pharmacotherapy Outcome and Monitoring Survey) cohort [34]. In mental health care organisations in the North of the Netherlands, it is routine care that ROM trained nurses invite patients annually for a ROM screening including somatic and psychosocial measures. Data of these measurements are reported in patients’ record forms and discussed with the patient. These data are stored in a large database and anonymized data are available for scientific research. This method was approved by the Medical Ethical Committee of the University Medical Center Groningen. For the LION study, data of two regular ROM screenings will be used for baseline and 12-months measures. An additional, short version of the ROM screening is scheduled six months after start of the intervention and patients will receive a small fee (€5,00/£4,30) for participation. ROM nurses carrying out the assessments are blinded for study allocation.

General data on birth year, gender, diagnosis, duration of illness and use of medication are derived from patient record forms.

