#### Mental health

During an interview, trained nurses administer positive and negative symptoms with the PANSS (Positive and Negative Syndrome Scale [35]) and depressive symptoms with the CDSS (Calgary Depression Scale for Schizophrenia [36]). Prior to the interview, patients fill in the MANSA, a self-report questionnaire about patients’ Quality of Life [37] and uncertainties can be discussed during the interview. The HoNOS (Health of the Nations Outcome Scale [38]) is an observation scale of psycho-social functioning and is scored by the case manager or team.

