### Statistical analysis

Variables will be presented as mean ± standard deviation (SD), and if not normally distributed as median [25th-75th percentiles], or N (%) for frequencies. Missing data are handled differently based on amount and type of missingness. If missing data can be well predicted by regression methods, multiple imputation will be considered. Otherwise, interpolation or replacement by study mean or median will be preferred over complete case analyses.

The primary outcome is the change in waist circumference (in cm) over time (from baseline to six and from baseline to twelve months) comparing the intervention group to the control group. This will be analysed with multilevel linear mixed models using teams as cluster. Analysis will be based on intention-to-treat principle. In per-protocol analyses, the intervention effect on cardiometabolic risk factors will be studied as described above, comparing participants with different degrees of intervention adherence to controls. Secondary study outcomes are analysed according to the same principles and techniques as the primary outcome. A priori sensitivity analyses are foreseen for participants’ age, gender and type of housing. In additional analyses, we will test whether the 12-months lifestyle intervention changes the level of motivation (stage-of-change) for changing diet of physical activity levels. An alpha of 0.05 is considered statistically significant.

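### The six-month part of research question 2 cannot be answered, because CDSS and PANSS are scheduled only at baseline and twelve months; the twelve-month part rests on the teams that administer each scale

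*Protocol article*

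**What the plan says.** All references are to the protocol article.

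- **Aims of the trial.** Secondary research question 2 asks whether the intervention is "effective in reducing depressive and negative symptoms in SMI patients after six and twelve months intervention compared to care as usual".
- **Mental health.** By interview, "trained nurses administer positive and negative symptoms with the PANSS"; depressive symptoms are rated with the CDSS.
- **Outcomes, Table 4.** The table is introduced with "An overview of all measurements at baseline, six and twelve months is given in Table 4". The CDSS and PANSS rows are marked at baseline and twelve months, and their six-month cells are empty.
- **Table 4, footnote b** (attached to the psychological measures as a group): "The conducted psychosocial measures within the ROM protocol could vary per team, not all teams conduct every psychosocial measure".
- **Measurements on patient level.** For this trial, "data of two regular ROM screenings will be used for baseline and 12-months measures". For the middle time point, "An additional, short version of the ROM screening is scheduled six months after start of the intervention".
- **Statistical analysis.** The primary outcome is change "from baseline to six and from baseline to twelve months", and "Secondary study outcomes are analysed according to the same principles and techniques as the primary outcome". On missing data, multiple imputation is considered where regression predicts the missing values well. Failing that, the plan prefers interpolation, or filling with the study mean or median, to a complete-case analysis.

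**The concern.** A stated research question names a time point at which its outcome is not measured. An unseen analysis plan cannot repair this, because it cannot analyse scores that the schedule does not collect.

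The analysis text adds two risks. Secondary outcomes are to be handled like the primary outcome, which has a six-month contrast. The fallback for missing data also favours filling in values over leaving them out. Read literally, these rules would allow a six-month symptom result with no six-month data behind it. They would also allow constant values to be entered for whole teams that never used a scale. The first would present one result as two, and the second would bias the twelve-month estimate towards no effect.

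**Working it through.** **Step 1. Question against schedule.**

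| Contrast asked for in question 2 | CDSS and PANSS scheduled? | Can it be estimated? |
|---|---|---|
| Baseline to six months | Baseline yes, six months no | No |
| Baseline to twelve months | Both yes | Yes, in teams that administer the scale |

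The empty cells are unlikely to be an extraction fault. In the same table, the physical measures, laboratory tests, care consumption questionnaire, SF6D, SQUASH and food frequency questionnaire carry three marks each, while the four psychological scales and medication use carry two. The text agrees: the two regular screenings supply baseline and twelve months, and the six-month visit is a short version. No other instrument for depressive or negative symptoms is scheduled at six months.

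**Step 2. What interpolation would produce.** Let x0 and x12 be a patient's scores at baseline and twelve months.

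- Interpolated six-month score: (x0 + x12)/2.
- Interpolated six-month change: (x0 + x12)/2 − x0 = (x12 − x0)/2.

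Every six-month change is half the twelve-month change. The arm difference and its standard error are both halved, so the test statistic is the same as at twelve months. Filling with a study mean or median cannot supply six-month scores, because no six-month mean or median exists.

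**Step 3. What mean filling for non-collecting teams would do at twelve months.** Let p be the share of patients in collecting teams (equal in both arms), d the true arm difference in change, and m the pooled mean change that is filled in.

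- Arm mean after filling: p × (arm's own mean) + (1 − p) × m.
- Difference after filling: p × d, because the m terms cancel.

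With p = 0.75 the estimate is 0.75d; with p = 0.50 it is 0.50d. The documents do not give p, so these values are assumptions. A median fill that is the same in both arms gives the same result.

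**Step 4. What restricting to collecting teams costs.** The plan has no power figure for symptoms. Its waist-circumference figure reproduces: 125 per arm (250 analysed, equal split assumed), a 5.8 cm difference and an SD of 16.3 cm give power 0.803, against the stated 80% or so. On the same base, with no clustering and equal loss in both arms, the standardised difference detectable with 80% power is (1.960 + 0.842) × √(2/n), with n = 125p per arm:

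| Assumed coverage p | n per arm | Detectable difference (SD) | Standard error relative to full coverage, 1/√p |
|---|---|---|---|
| 100% | 125 | 0.35 | 1.00 |
| 75% | 93.75 | 0.41 | 1.15 |
| 50% | 62.5 | 0.50 | 1.41 |
| 25% | 31.25 | 0.71 | 2.00 |

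Incomplete coverage costs precision. It does not remove the twelve-month comparison.

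**The case against.** The strongest reply is that this is a slip of phrasing in a secondary question. In the hypotheses that follow the aims, six and twelve months are attached to waist circumference, BMI and the metabolic syndrome score, and no time point is given for symptoms. The wording of question 2 may simply have been carried over from question 1. Likewise, the sentence on secondary outcomes may mean only the same model and the intention-to-treat principle, without both time contrasts. Scores that were never scheduled are also not missing data in the usual sense, and nothing says that anyone plans to interpolate them. Much of this stands: the interpolation result describes what the rule would allow, not what is announced. The mismatch remains, because the question as printed names six months. The missing-data rule also has no exception for measures that a team does not use.

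A reader might infer two stronger claims that the document does not support.

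- **That question 2 as a whole cannot be answered.** Both scales are scheduled at baseline and twelve months, so the twelve-month effect can be estimated.
- **That uneven use of the scales breaks the randomised comparison.** Footnote b covers four instruments together. It does not say that CDSS or PANSS is the one left out, in how many teams, or that use differs by arm. It describes scale use as a feature of a team's routine monitoring. If that feature pre-dates allocation, restricting to collecting teams keeps a randomised comparison, and any imbalance between arms is chance. Bias would need scale use to change because of allocation, and nothing suggests that.

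The coverage limit is also disclosed: besides the footnote, the section on potential risks for bias says that sites may lack capacity for all measures.

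**Conclusion.** The point holds in a limited form. The six-month part of question 2 has no planned data and cannot be answered. This follows from the document alone and needs no assumption.

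The twelve-month part can be answered from the teams that administer each scale. Coverage is a disclosed limit on precision and generalisability, of unknown size. If 75% or 50% of patients were covered, the standard error would rise by about 15% or 41%.

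The missing-data rule as written is unsuitable in both places. Interpolation would report half the twelve-month effect as a six-month finding. Mean or median filling for non-collecting teams would shrink the twelve-month difference to about p times its size. That result assumes equal coverage in both arms and one common filled value. The primary outcome and the sample size are not affected.

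**What to change.** 1. Limit research question 2 and its analysis to twelve months. Alternatively, reconcile the schedule with the question by adding both scales to the six-month assessment.
2. If the schedule stays as it is, state that six-month symptom scores are not collected and will not be interpolated.
3. State that each scale is analysed in the teams that collect it, with no mean or median filling for teams that do not, and report which teams those are.

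With the twelve-month limit, the cost is a few lines of wording. The six-month symptom claim is dropped, and the twelve-month result applies to the collecting teams. Adding the scales at six months would keep the claim, at the price of longer interviews at a visit designed to be short.

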## Methods

The Lifestyle Interventions for severe mentally ill Outpatients in the Netherlands (LION) trial is a pragmatic single-blind multi-site cluster randomised controlled trial (RCT). Details are described below according to the SPIRIT 2013 statement [29]. The study was approved by the Medical Ethical Committee of the University Medical Center Groningen. The trial is registered in the Dutch Trial Registry NTR3765 (www.trialregister.nl, 21 December 2012).

### Study setting

Mental health care for severe mentally ill (SMI) outpatients is organized by a Flexible Assertive Community Treatment (FACT) team with MH nurses. FACT means that patient care is outreaching, takes place in the community (patients’ own environment) and ranges from high intensive (24 h) treatment to low intension support – for a detailed description of FACT, see [30, 31]. Patients living in sheltered facilities receive a combination of housing and services in the community. 21 FACT and eight sheltered facility teams serving SMI patients of five mental health care organizations in the North of the Netherlands, an area covering 2.8 million inhabitants, are invited for this study. Per team, nurses are invited to participate. All teams per organization are matched based on caseload size, mean age of patients, mean duration of admission of patients, most frequent diagnosis and location (urban or rural). After matching, teams are randomly allocated to the control or intervention arm by means of a random number generator by a researcher of the research team not involved in training of staff and recruitment of patients (see Fig. 1 for flowchart of the study). To minimise spill-over, randomisation is on team level, although inclusion of study participants and statistical inference are on patient level.

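### Teams are matched within five organisations before randomisation, but the stated primary model names only team as cluster and keeps type of housing for sensitivity analysis, which may cost some power

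*Protocol article*

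**What the plan says.** **Allocation (Protocol article, Study setting).** The trial invites "21 FACT and eight sheltered facility teams serving SMI patients of five mental health care organizations in the North of the Netherlands", which makes 29 clusters. On the matching, the section says: "All teams per organization are matched based on caseload size, mean age of patients". The other listed factors are how long patients have been admitted on average, the commonest diagnosis, and whether the team is urban or rural. The next step is: "After matching, teams are randomly allocated to the control or intervention arm by means of a random number generator". The text does not say whether the matched sets are pairs or larger groups. Team type (FACT or sheltered) is not among the listed matching factors.

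**Analysis (Protocol article, Statistical analysis).** "The primary outcome is the change in waist circumference (in cm) over time (from baseline to six and from baseline to twelve months"), compared between arms. On the model: "This will be analysed with multilevel linear mixed models using teams as cluster". Organisation, matched set and team type are not named. On setting, the section says: "A priori sensitivity analyses are foreseen for participants’ age, gender and type of housing". Type of housing is the listed variable closest to team type, and it is placed outside the primary analysis.

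**The concern.** When an allocation is restricted within groups, the usual principle is to analyse within those groups. Matching within organisation removes between-organisation differences from the comparison of arms. A model that knows only about teams still counts those differences as random team-to-team noise. If organisations differ in how waist circumference changes, the model-based standard error is then larger than the true sampling variability. The test is conservative, and the precision gained by the design is not used.

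Team type raises a related issue. It is not a stated matching factor, only eight teams are sheltered, and setting could plausibly affect diet and activity. A chance imbalance between arms is therefore possible, and the stated primary model names no term that would adjust for it.

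This trial has little precision to spare. The section on changes in study design says that clustering was dropped from the sample size calculation, so any ICC above zero already puts power below the planned level.

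**Working it through.** **The plan's own figure.** Inputs from the Participants section: difference 5.8 cm, SD 16.3 cm, 250 evaluable patients (125 per arm), two-sided alpha 0.05.

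- SE = 16.3 × √(2/125) = 2.062 cm; 5.8/2.062 = 2.813.
- Power = Φ(2.813 − 1.96) = 0.803 (0.800 with the noncentral t).

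The stated power of about 80% reproduces. It contains no loss from clustering and no gain from matching, so this point does not make that figure wrong.

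**Effect of adding organisation and team type.** Inputs:

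- 29 teams, 14.5 per arm on average; m = 250/29 = 8.62 patients per team. Equal team sizes and full participation are assumed.
- ICC (ρ) of the change in waist circumference: not in the documents. Range used: 0.01 to 0.10.
- Share r of between-team variance explained by organisation and team type: not in the documents. Values used: 0, 0.2 and 0.5.
- Team-level df: 29 − 2 = 27 without the terms; 27 − 4 − 1 = 22 with them. Critical t: 2.052 and 2.074, ratio 1.0107.

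Formulas, per team mean in units of the total variance:

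- without the terms, V0 = ρ + (1 − ρ)/m
- with the terms, V1 = ρ(1 − r) + (1 − ρ)/m
- SE = 16.3 × √(2V/14.5)
- interval-width ratio = √(V1/V0) × 1.0107

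The SD cancels from the width ratio. The formula takes the added terms as balanced between arms.

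Worked case, ρ = 0.03 and r = 0.5: V0 = 0.03 + 0.97/8.62 = 0.1425; V1 = 0.015 + 0.1125 = 0.1275; V1/V0 = 0.895; square root 0.946; × 1.0107 = 0.956.

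| ICC | V1/V0, r = 0.5 | Width ratio, r = 0.5 | Width ratio, r = 0.2 | Power without terms (27 df) | Power with terms (22 df), r = 0.5 |
|---|---|---|---|---|---|
| 0.01 | 0.960 | 0.990 | 1.003 | 74.4% | 75.3% |
| 0.03 | 0.895 | 0.956 | 0.989 | 68.7% | 72.7% |
| 0.05 | 0.844 | 0.929 | 0.979 | 63.6% | 70.2% |
| 0.10 | 0.755 | 0.878 | 0.960 | 53.3% | 64.5% |

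If the terms explain nothing (r = 0), the interval is 1.1% wider at every ICC. Break-even needs V1/V0 = 1/1.0107² = 0.979, that is r = 0.021 × V0/ρ. This gives about 26% explained at ICC 0.01, 10% at 0.03 and 7% at 0.05.

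**Effect of matched-set terms, if the sets are pairs.** About 13 df remain, with critical t 2.160 and ratio to the 27-df value 1.053. With r = 0.5 the width ratio is 1.032 at ICC 0.01, 1.013 at 0.02, 0.996 at 0.03 and 0.967 at 0.05. Pair terms therefore lose precision at low ICC and roughly break even at 0.03.

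**The case against.** The strongest reply is that the article names the clustering level and does not list the fixed effects. It excludes nothing, it is a condensed account, and covariates are often left to an analysis plan that is not shown here. That stands in part: one may say that the stated model names neither organisation nor team type, but not that the final model will omit them. The point goes beyond missing detail because the article describes a restricted allocation, states a primary model that does not reflect it, and explicitly assigns the variable closest to team type to sensitivity analysis.

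It is also fair that the stated model includes the randomised unit, that leaving out the matching makes inference conservative, and that the gain rests on quantities the documents do not give. All of this stands and limits the point to efficiency.

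A reader might go further in three ways that the documents do not support.

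- **A biased or invalid test.** Matching balances the listed factors by design. The outcome is change from baseline, so baseline differences in waist circumference between settings are already subtracted. Type I error is not inflated.
- **A probability of imbalance.** Drawing 14 of 29 teams with no restriction puts the chance that the eight sheltered teams split 6:2 or worse at about 21%. That calculation ignores the matching within organisation, which may separate the two team types in part. Without the matched sets, the probability cannot be computed.
- **A size for the resulting shift.** A 6:2 split gives 6/14.5 − 2/14.5 = 0.28, so a 3 cm difference between settings would move the estimate by about 0.8 cm. The 3 cm has no source. It would have to be a difference in change, and it is more than half of the 5.8 cm target.

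**Conclusion.** The point holds as one of efficiency and clarity, with moderate confidence. The allocation is restricted within organisation, and the stated primary analysis does not use that restriction. If organisation and setting predict change in waist circumference, the confidence interval is wider than it needs to be.

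The gain from the two terms is modest at the lower ICCs and could be nil. It depends on an assumed ICC and on an assumed half of the between-team variance being explained, and it shrinks or vanishes when less is explained. Chance imbalance of the eight sheltered teams is possible but cannot be quantified from the article. The case covers organisation and team type. It does not extend to requiring matched-set terms in the model.

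**What to change.** State in the primary model, and in the models for the other outcomes that follow the same principles, fixed effects for organisation (five levels, 4 df) and team type (FACT versus sheltered, 1 df), with team kept as the random cluster effect. Fix this before unblinding, so that there are not two defensible estimates, one adjusted for setting and one not, with no pre-specified choice between them. Say how the matched sets were formed. Use matched set only in a re-randomisation check that repeats the allocation within the sets, and do not make it a required model term.

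The cost is wording plus about 5 of 27 team-level degrees of freedom, which moves the critical t from 2.05 to 2.07. In the worst case, where the terms explain nothing, the interval is about 1% wider.
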